## Abstract

**Background:**

Caesarean section (CS) has short and long-term health effects for both the woman and her baby. One of the greatest contributors to the CS rate is elective repeat CS. Vaginal birth after caesarean (VBAC) is an option for many women; despite this the proportion of women attempting VBAC remains low. Potentially the relationship that women have with their healthcare professional may have a major influence on the uptake of VBAC. Models of service delivery, which enable an individual approach to care, may make a difference to the uptake of VBAC. Midwifery continuity of care could be an effective model to encourage and support women to choose VBAC.

**Methods/Design:**

A randomised, controlled trial will be undertaken. Eligible pregnant women, whose most recent previous birth was by lower-segment CS, will be randomly allocated 1:1 to an intervention group or control group. The intervention provides midwifery continuity of care to women through pregnancy, labour, birth and early postnatal care. The control group will receive standard hospital care from different midwives through pregnancy, labour, birth and early postnatal care. Both groups will receive an obstetric consultation during pregnancy and at any other time if required. Clinical care will follow the same guidelines in both groups.

**Discussion:**

This study will determine whether midwifery continuity of care influences the decision to attempt a VBAC and impacts on mode of birth, maternal experiences with care and the health of the neonate. Outcomes from this study might influence the way maternity care is provided to this group of women and thus impact on the CS rate. This information will provide high level evidence to policy makers, health service managers and practitioners who are working towards addressing the increased rate of CS.

**Trial registration:**

This trial is registered with the Australian New Zealand Clinical Trials Registry (ANZCTR): ACTRN12611001214921

## Background

The rate of caesarean section (CS) in Australia has increased over the past decade and is now well above many similar countries [1,2]. One of the greatest contributors to the overall CS rate is a woman having an elective repeat CS (ERCS) [1]. In one Australian state, 76% of those with a previous CS who give birth at term have another CS, and one third of all CS involves women who have had a previous CS [1]. A National Review of Maternity Services undertaken in Australia highlighted concerns around the high rates of caesarean section and recommended that the Australian government “initiate targeted research aimed at improving the quality and safety of maternity services in select key priority areas, such as evidence around interventions, particularly caesarean sections” (page 14) [2].

Concerns about a high CS rate centre around growing evidence of increasing maternal morbidity associated with such operations for women, such as increased blood loss, blood clots, abdominal organ injury, need for hysterectomy and longer hospital stays [3-6]. Repeat CS has also been associated with significantly higher maternal and neonatal morbidity and mortality compared with caesarean or vaginal births for women who do not have a prior CS [5,7-10]. Babies born by CS are at risk of respiratory distress syndrome [11], persistent pulmonary hypertension and admission to a neonatal intensive care unit [12,13]. Neonatal mortality rates have been reported to be 1.7 to 1.9 times higher amongst babies born by CS compared with those born vaginally [14]. Previous CS has also been associated with an increased risk of stillbirth [15].

As an alternative, women who have had a previous lower-segment CS, and an uncomplicated pregnancy, can be offered to attempt a vaginal birth after CS (VBAC) [16]. However, a cross-sectional study undertaken in one Australian state (New South Wales) showed that, despite this, the rate of VBAC declined significantly between 1998 and 2006 (from 31% to 19%, respectively) and the proportion of women who attempted a vaginal birth also declined (from 49% to 35%, respectively) [17]. In this study, more than half the women (59%) who attempted VBAC were successful [17].

The best available international evidence suggests that VBAC does not increase the risk of hysterectomy or maternal mortality [18]. Neonatal mortality rate, after adjustments are made for pre-existing fetal anomalies, has been reported to be 24 per 10,000 for women who planned a VBAC compared with 9 per 10,000 for those who planned a repeat CS [18]. Although this results in an increased risk, the absolute risk is small, and comparable to the background risk of neonatal mortality for women having their first baby [19]. In the USA, a large prospective observational study involving nearly 46,000 women showed that planned VBAC was associated with a 1% increased risk of a blood transfusion, a 1% increased risk of endometriosis, and a 0.7% risk of symptomatic uterine rupture. Rates of uterine rupture for women who undergo a planned VBAC have been reported to be in the range of 22–74 per 10,000, compared with a risk of 0.5–2 per10,000 births in women with non-scarred uteri [1,19]. Other evidence shows a lesser increase in risk of perinatal mortality for VBAC, with a risk difference of 1.5 per 10,000 births compared with repeat caesarean section [20]. Therefore offering women the opportunity to attempt VBAC, in an appropriately staffed and resourced maternity unit, is a safe and ethical innovation to test.

Whereas no studies have examined the effects of midwifery continuity of care, some research has examined what influences women to choose VBAC. One study from the USA showed that the major influences were the woman’s sense of control in the decision-making process and the clinician’s encouragement of VBAC [21]. Whereas these were not linked to a model of care, it is well established that midwifery continuity of care programs increase women’s sense of control over decision making, [22] hence the logical link in our hypothesis. Two randomised controlled trials evaluating different antenatal education interventions designed to increase VBAC rates have been published and neither intervention altered VBAC rates [23,24]. One of the studies showed that consistent information using a decision-aid booklet reduced decisional conflict [25]. We plan to build on this evidence by providing consistent antenatal information from a small group of midwives, together with continuity of care in labour and birth.

### The intervention: midwifery continuity of care

Midwifery continuity of care allows women to develop a relationship with the same caregivers throughout pregnancy, birth, and the postnatal period. Women have a midwife caring for them during labour and birth whom they have met before and feel that they know, and this trusting relationship increases their confidence [26,27]. Women with a previous CS are often included in trials of midwifery continuity of care although they have not been specifically studied or targeted.

Midwifery continuity of care per se has been widely studied. A systematic review in the Cochrane Library examining midwifery continuity of care included 11 trials (12,276 women). Women who had midwife-led models of care were less likely to use regional analgesia (RR 0.81, 95% CI 0.73–0.91) or have an instrumental birth (RR 0.86, 95% CI 0.78–0.96), and were more likely not to use intrapartum analgesia/anaesthesia (RR 1.16, 95% CI 1.05–1.29), experience spontaneous vaginal birth (RR 1.04, 95% CI 1.02–1.06), feel in control during labour and childbirth (RR 1.74, 95% CI 1.32–2.30), and initiate breastfeeding (RR 1.35, 95% CI 1.03–1.76) [22]. Three trials have shown that midwifery continuity of care significantly reduced the CS rate: one small trial in Canada [28] and two in Australia, the most recent being published in 2012 [29,30].

In preliminary work for this trial, we reviewed the outcomes of a midwifery continuity of care program at one NSW hospital and compared the VBAC rate in the program with the rates in the area health service (AHS) in which the hospital is situated. The rate of attempted VBAC was 62.5% in the midwifery continuity of care program compared with 27% for the AHS and the vaginal birth rate was considerably higher in the program (76% and 54%, respectively). There was no increase in adverse outcomes for mothers or babies, although the total numbers in this evaluation were small (n = 377) (unpublished data). These data, although from a small number of women, provide some evidence to support the hypothesis to be tested in this trial, that is, that midwifery continuity of care will increase the proportion of women who attempt VBAC, increasing the overall rate of vaginal birth and reducing the CS rate.

## Methods/Design

The study uses a two arm, un-blinded randomised controlled design, to compare the outcomes for women who had midwifery continuity of care compared with those who had standard maternity care.

### Aim and objectives

The primary aim is to determine whether midwifery continuity of care for women with a previous CS increases the proportion of women who attempt vaginal birth in their current pregnancy. The primary hypothesis is that women with a previous CS, who are eligible for a vaginal birth and receive midwifery continuity of care, will be 50% more likely to choose to attempt a vaginal birth in their current pregnancy than similar women receiving standard care.

The secondary aims are to determine whether midwifery continuity of care increases the proportion of women experiencing a vaginal birth, and affects neonatal health or the emotional outcomes for women; and to explore the differences in women’s experiences of care and the decision making processes between the groups.

### Study population

All eligible women booking maternity care at two study sites in Australia will be invited to participate.

### Sample size

Our study of VBAC in NSW [17] showed that only 35% of women who are eligible for a vaginal birth following one previous CS attempted VBAC. The trial is designed to detect a clinically significant increase in the primary outcome, attempted VBAC, from 35% to 52.5%. In order to detect this difference 274 women will be required, providing 80% power with α = 0.05. To allow for a 15% loss to follow-up, a total of 332 women will be required, 166 in each group. This sample size will also be sufficient to demonstrate a significant improvement in VBAC success rates from 53% to 70.5% (n = 262).

The data informing the sample size calculations are drawn from a published cross-sectional study using population-based data from NSW [17,31] and descriptive data from the Obstetrix perinatal database at one of our study sites. Currently, midwives at this hospital providing continuity of care to women eligible for a VBAC are achieving attempt rates of 62.5% and success rates of 76%.

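### The sample is said to suffice for VBAC success (53% vs 70.5%, n = 262), but 262 counts women who attempt; at the plan's attempt rates, power is about 42–51%, not 80%

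*Protocol article*

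**What the plan says.** The Sample size section powers the trial on attempted VBAC: "The trial is designed to detect a clinically significant increase in the primary outcome, attempted VBAC, from 35% to 52.5"%. It continues: "In order to detect this difference 274 women will be required, providing 80% power with α = 0.05". Loss is then added: "To allow for a 15% loss to follow-up, a total of 332 women will be required, 166 in each group".

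The next sentence extends the claim to a second outcome: "This sample size will also be sufficient to demonstrate a significant improvement in VBAC success rates from 53% to 70.5"% (n = 262). The same section describes midwives at one study site as "achieving attempt rates of 62.5% and success rates of 76"%. The Background reports from the state-wide study that "more than half the women (59%) who attempted VBAC were successful".

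Among the secondary aims, Aim and objectives asks whether the intervention "increases the proportion of women experiencing a vaginal birth".

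**The concern.** A woman can have a successful VBAC only if she attempts one. The figure of 262 is a two-arm requirement in which every counted woman contributes a success or a failure. The protocol sets it against the number of women enrolled, most of whom are not expected to attempt under the plan's own rates. Nothing in the section inflates 262 for the women who do not attempt.

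This is the only secondary comparison for which the protocol claims adequate size. A reader who trusts the claim could take a non-significant difference in success as evidence of no effect, when the chance of detecting the assumed difference was about one in two.

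**Working it through.** **Inputs.** All are from the Sample size section unless noted.
- Success 53% vs 70.5%; n = 262, or 131 per arm.
- Attempt rates 35% and 52.5%.
- Power 80%, α = 0.05; 274 evaluable, 332 randomised, 15% loss. 332 × 0.85 = 282.
- 1:1 allocation (Group allocation section).
- Two-sided testing is an assumption. The protocol does not state sidedness, but the two-sided formula below reproduces its figures and one-sided versions do not.

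**Step 1: denominator of success.**
- The Background's 59% is explicitly a share of attempters.
- In the Sample size section, 76% success is paired with 62.5% attempting, so success cannot be a share of all women.
- If 35% of controls attempt, 53% of all controls cannot succeed.

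**Step 2: reproduce the plan's figures.** For proportions p1 and p2 with difference d and mean p̄:

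n = [1.96√(2p̄(1−p̄)) + 0.842√(p1(1−p1) + p2(1−p2))]² / d²

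With continuity correction: n′ = (n/4)[1 + √(1 + 4/(nd))]².
- 35% vs 52.5%: n = 124.96 and n′ = 136.15, so 137 per arm, 274 in total. This matches exactly.
- 53% vs 70.5%: n = 119.88 and n′ = 131.06, so 131 (262) to the nearest whole number or 132 (264) rounded up. Corrected power at 131 per arm is 79.98%.

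So 262 is the number of women with a success-or-failure outcome needed for 80% power.

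**Step 3: attempters expected.** With m women per arm, n1 = 0.35m and n2 = 0.525m.
- 274 women: 137 × 0.35 = 48 and 137 × 0.525 = 72; total 120.
- 282 women: 141 × 0.35 = 49 and 141 × 0.525 = 74; total 123.
- 332 women: 166 × 0.35 = 58 and 166 × 0.525 = 87; total 145.

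To obtain 262 attempters, the average attempt rate would have to be 262/274 = 96%, or 262/332 = 79% with no loss. The plan's average is (35 + 52.5)/2 = 43.75%.

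**Step 4: power among attempters.** Power = Φ[(d* − 1.96·s0)/s1]. Here d* = 0.175, less ½(1/n1 + 1/n2) if corrected; s0 is the pooled and s1 the unpooled standard error. For 274 women, s0 = 0.0898 and s1 = 0.0899. Uncorrected, z = −0.010. Corrected, d* = 0.1576 and z = −0.204.

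| Women | Attempters | Power, corrected | Power, uncorrected |
|---|---|---|---|
| 274 | 120 | 41.9% | 49.6% |
| 282 | 123 | 43.2% | 50.7% |
| 332, no loss | 145 | 50.4% | 57.4% |

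Simulation with random numbers of attempters gave 42.1% / 49.8% at 274 and 50.5% / 57.5% at 332.

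**Step 5: size needed for 80%.**
- Uncorrected: 100 + 150 attempters. 100/0.35 = 285.7, so 286 per arm, 572 evaluable; 572/0.85 ≈ 673 randomised.
- Corrected: 109 + 164 attempters. 109/0.35 = 311.4, so 312 per arm, 624 evaluable; 624/0.85 ≈ 734 randomised.

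**Step 6: vaginal birth among all randomised women, 274 evaluable.**
- Both rates as assumed: 0.35 × 0.53 = 18.6% vs 0.525 × 0.705 = 37.0%. Power is 91.1% corrected, 93.1% uncorrected.
- Only attempts rise: 18.6% vs 0.525 × 0.53 = 27.8%. Power is 38.8% corrected, 44.4% uncorrected.

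**The case against.** **The attempt rates may be too low.** The Exclusion criteria remove women who request an elective repeat caesarean at booking, so trial attempt rates could exceed 35% and 52.5%. This is fair, and the power figures are conditional on those rates. More favourable inputs still fall short over 274 to 332 women: 45–61% with 62.5% attempting in the intervention arm, 58–73% at an assumed 50% vs 75%, and 60–74% with 62.5% in both arms, which would mean no effect on the primary outcome.

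**The terminology is not uniform.** In the Background, the section on the intervention calls the 76% a vaginal birth rate and does not restrict it to attempters. That stands as an inconsistency of wording. It does not rescue the sentence, because 53% success among all controls is impossible with 35% attempting.

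**The sentence does not itself say 80%.** That is true. The 80% is inferred from the fact that 262 reproduces at that power with the formula that gives 274.

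**The fault is confined to one supporting sentence.** This stands too. No stated analysis or stopping rule depends on it.

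A reader might go further and infer that the protocol plans a biased test restricted to attempters, or that its secondary aim lacks power. The documents do not support either. The Analysis section specifies no attempters-only test and calls for intention to treat. The stated aim is the proportion having a vaginal birth, and success among attempters is not listed as an aim. Whether success among attempters would mislead in direction depends on how the additional attempters fare, for which the documents give no figure.

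**Conclusion.** The sufficiency claim is wrong as written. At the plan's own attempt rates, the trial yields about 120–123 attempters from 274–282 evaluable women, under half of the 262 needed. Power for 53% vs 70.5% is about 42–51%, and at most about 57% if no one is lost and no correction is used. This rests on two-sided α = 0.05, attempt rates of 35% and 52.5%, and success read as a share of attempters. The last is the only reading consistent with the protocol's figures.

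It would be a mistake to conclude that the trial as a whole is too small. The primary calculation reproduces and is unaffected. The all-women vaginal birth aim is well powered if both assumed rates hold, though not if only attempts rise.

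**What to change.** In the Sample size section, delete the sentence on VBAC success, or correct it to give the expected number of attempters and the resulting power. In its place, state the power for the secondary aim already in Aim and objectives, vaginal birth among all randomised women. With 274 evaluable women this is about 91–93% for 18.6% vs 37.0%, and about 39–44% for 18.6% vs 27.8% if only attempts rise. Both figures should appear, so that the dependence on the success assumption is visible.

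Report success among attempters descriptively. Attempting happens after randomisation and is what the intervention is meant to change, so the two sets of attempters are not a randomised comparison.

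The cost is a rewording and the withdrawal of the sufficiency claim for success among attempters. Recruitment and data collection stay as they are.

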### Control and intervention groups

#### Intervention

##### Midwifery continuity of care (CofC)

Women allocated to the intervention group will receive midwifery continuity of care from a small group of midwives.[27] The midwives provide care during the antenatal, labour and birth, and postnatal periods (to two weeks postnatal). Midwives will adhere to The National Midwifery Guidelines for Consultation & Referral [32]. All women will have an appointment with an obstetric consultant during pregnancy (to re-assess VBAC suitability and discuss the birth plan). If a woman develops complications during pregnancy and requires additional care, she will continue with the midwifery continuity of care model while also attending obstetric or other consultations (this is the same for both groups). Labour and birth care will be provided at the hospital’s birth unit/labour ward and postnatal care will be provided in hospital or the woman’s own home following discharge from hospital.

#### Control

##### Standard midwifery care

Women allocated to the control group will receive the current model of public maternity care at the two study sites. Antenatal care is provided by antenatal staff (midwives and obstetricians). Staff in the Birth Unit provides labour and birth care and midwives in the postnatal ward provide postnatal care. Women are also offered midwifery visits at home following discharge from hospital (4–48 hours after a vaginal birth). All these care providers are different people.

### Inclusion criteria

● Most recent birth was by lower-segment CS

● No more than one previous CS

● Considered low risk, other than a history of one previous CS

● No other previous uterine incision

● No previous uterine rupture

● No contraindications for vaginal birth at the time of enrolment

● English proficiency (spoken and written)

● Public patient

● No known preference for a certain model of care, such as: GP-shared care or midwifery continuity of care

### Exclusion criteria

● Women who reside outside the hospital postnatal home-visiting zone

● Women who specifically request an ERCS at booking in

● Women with BMI > 35

### Trial recruitment

Women telephone the booking office to book for maternity care and receive an appointment for their first/booking-in visit. The women will be initially screened by the booking clerk for eligibility into the trial according to the eligibility criteria. An information pack about the study is posted to all eligible women. At the first/booking-in visit, the research assistant (RA) approaches each eligible woman and asks if she received the information and whether she is interested in participating. If the woman agrees, the consent form is signed and the woman is registered as a trial participant and the remote telephone allocation service at the university is contacted for random allocation.

### Group allocation

Randomisation will be on a 1:1 basis. Allocation concealment will be assured by using a remote telephone allocation service through the university research department. The RA will telephone the university to provide the woman’s initials, medical record number and date of birth. The clerk at the university campus will allocate women based on a randomization schedule developed independently from the RA. The midwife will be informed of the group to which the woman has been allocated and will receive her study number, which will be recorded in the Trial Register and Log Book. If allocated to standard care, the woman will be advised of her next clinic appointment. If allocated to midwifery continuity of care, she will be advised that the continuity of care midwives will contact her with a suitable appointment time.

### Data collection

#### Clinical data

The majority of clinical data required for the study are routinely collected and available in hospital records. The RA will collect these data and 5% of the records will be double checked by one of the CIs to verify their accuracy and consistency.

### Maternal

#### Demographic

● Age

● Parity

● Previous pregnancy outcomes

● Socio-economic status (derived from postcode, marital and employment status,)

● Past medical, surgical and obstetric risk factors

#### Pregnancy

● Complications during pregnancy

● Planned mode of birth prior to labour/CS

#### Labour and birth

● Syntocinon augmentation

● Artificial rupture of membranes

● Immersion in water for pain relief

● Epidural or spinal anaesthesia

● General anaesthetic

● Mode of birth

● Uterine rupture or scar dehiscence

● Major postpartum haemorrhage > 1000 mL and/or requiring operative procedure and/or blood transfusion

● Length of hospital stay

● Readmission Admission to ICU/HDU

● Maternal death (within 42 days)

#### Neonatal

● Apgar score < 7 at 5 min

● Admissions to neonatal unit within 48 hours of birth for at least 48 hours with feeding difficulties or respiratory distress

● Readmission to hospital

● Breastfeeding within 1 hour of birth

● Skin to skin contact within one hour of birth

● Mode of feeding at 6 weeks

● Stillbirth and neonatal death (within first 28 days)

